## Abstract

**Background:**  Dengue is a disease of major global importance. While most symptomatic infections are mild, a small proportion of patients progress to severe disease with risk of hypovolaemic shock, organ dysfunction and death.  In the absence of effective antiviral or disease modifying drugs, clinical management is solely reliant on supportive measures. Obesity is a growing problem among young people in Vietnam and is increasingly recognised as an important risk factor for severe dengue, likely due to alterations in host immune and inflammatory pathways. Metformin, a widely used anti-hyperglycaemic agent with excellent safety profile, has demonstrated potential as a dengue therapeutic
*in vitro* and in a retrospective observational study of adult dengue patients with type 2 diabetes.  This study aims to assess the safety and tolerability of metformin treatment in overweight and obese dengue patients, and investigate its effects on several clinical, immunological and virological markers of disease severity.

**Methods:** This open label trial of 120 obese/overweight dengue patients will be performed in two phases, with a metformin dose escalation if no safety concerns arise in phase one. The primary endpoint is identification of clinical and laboratory adverse events.  Sixty overweight and obese dengue patients aged 10-30 years will be enrolled at the Hospital for Tropical Diseases in Ho Chi Minh City, Vietnam. Participants will complete a 5-day course of metformin therapy and be compared to a non-treated group of 60 age-matched overweight and obese dengue patients.

**Discussion:**  Previously observed antiviral and immunomodulatory effects of metformin make it a promising dengue therapeutic candidate in appropriately selected patients. This study will assess the safety and tolerability of adjunctive metformin in the management of overweight and obese young dengue patients, as well as its effects on markers of viral replication, endothelial dysfunction and host immune responses.

**Trial registration:** ClinicalTrials.gov:
 NCT04377451 (May 6
^th^ 2020).

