## Background

Dengue is a major threat to global public health, with an estimated annual incidence of 390 million infections worldwide, leading to approximately 96 million symptomatic cases and 22,000 deaths in more than 120 countries
^1^. Despite increasing understanding of dengue pathogenesis, effective anti-viral or disease modifying agents are yet to be identified, and patient management remains reliant on judicious fluid replacement in response to plasma leakage during the critical phase of illness (usually days 4–6)
^2,
3^.

While the vast majority of symptomatic infections give rise to the milder form of disease, dengue fever, those that progress to severe disease carry significant risk of vital organ dysfunction and death. Several patient groups have been identified as being at particular risk of severe dengue, including the elderly, pregnant women, those with comorbid illness, and those with prior exposure to alternative dengue serotypes
^4^. An important and increasingly recognised severe dengue risk factor is obesity, a condition which has had a dramatic increase in prevalence among Vietnamese children and adolescents over the last two decades
^5^. Several observational studies have reported an association between obesity and severe dengue
^6–
9^. A recent systematic review and meta-analysis reported the odds of developing severe dengue to be significantly higher in obese children in comparison to their non-obese counterparts (OR = 1.38; 95%CI 1.10 - 1.73)
^10^.

The underlying mechanism remains unknown, but could possibly be explained by chronic low-grade inflammation that is induced by being overweight or obese
^11,
12^. Adipocytes are known to produce pro-inflammatory cytokines and adipokines, such as adiponectin, resistin and leptin, each of which have a role in immunomodulation. Obesity-induced leptin and resistin are known to be associated with many of the physiological abnormalities seen in dengue, including platelet dysfunction, vascular inflammation, myocardial injury, endothelial dysfunction
^13–
16^, and capillary hyper-permeability
^17–
19^. Additionally, it is possible that more severe infection is permitted by altered CD8
^+^ T cell immunity and impairment of natural killer (NK) cell activity in obese hosts
^20,
21^.

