### Design

This is an open-label study investigating metformin therapy in 60 overweight and obese Vietnamese adults (30 patients) and children (30 patients). Age range of 10 to 30 years, who are admitted to the Hospital for Tropical Diseases (HTD) in Ho Chi Minh City (HCMC), Vietnam, with positive non-structural protein 1 (NS1) rapid test and onset of fever <72 hours prior to admission.

We will investigate the effects of five days of metformin treatment on the grounds that the critical phase of disease usually occurs around the fifth day of illness.

The trial will be conducted in two phases, with a dose escalation between phases (
Figure 1). In the initial phase (cohort 1), five young adults (age ≥16) and five children (age <16) with body mass index (BMI) >25 kg/m
^2^ (BMI-for-age >1 standard deviation – SD) will be provided with a low dose of metformin once daily at 850mg and 500mg, respectively. If the five-day safety and clinical data of cohort 1 show no safety concerns, the study will progress to the second phase (cohort 2). This will include 25 adults and 25 children, who will be given a weight-based dose of metformin; 1000mg (500mg twice daily) for participants with weight <60kg, and 1500mg (1000mg mane, 500mg nocte) for those ≥ 60kg. Of note, the actual number of patients in each cohort will depend on the results of safety reviews. Recruitment is expected to happen over two dengue seasons, and discharged patients will be asked to return for a single outpatient follow-up (FU) visit around day 28 of illness.

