**Figure 1. f1:**
[figure not shown]
Trial flow chart.

The 60 patients receiving treatment will be compared to 60 overweight or obese patients with standard of care (without treatment) recruited contemporaneously from the same wards, with the same enrolment criteria, in an ongoing observational study as the control arm.

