### Data collection

***Clinical evaluation.*** Patients will be reviewed daily until discharge. All clinical symptoms and signs will be recorded in the CRF. An ultrasound scan will be performed on day 5–6 of illness to detect evidence of fluid accumulation. General management decisions will be at the discretion of the attending ward doctors. Details of all AEs and SAEs will be recorded on specific forms, together with an assessment as to whether the events are likely to have been related to any treatment received. All SAEs will be reported promptly to the DMC and ECs according to policy.

***Laboratory evaluation.*** Full blood count (FBC) and POC glucose and lactate tests will be undertaken daily until discharge. An additional POC glucose test will be performed before their evening meal.

In addition, levels of serum albumin, transaminases (ALT/AST), creatinine, total cholesterol, HDL-cholesterol, LDL-cholesterol, triglycerides, and C-reactive protein (CRP) will be measured on alternate days. All tests will be done more frequently when clinically indicated.

Research samples collected daily until discharge will be used for dengue diagnostics (NS1 antigen detection and PCR assays). Residual blood from FBC samples will be collected for daily plasma viraemia levels. Serology tests (Capture IgM/IgG ELISAs) will be performed on enrolment (acute) and discharge/FU (convalescent) samples. Other laboratory investigations will include endothelial, inflammatory and lipid biomarkers (VCAM1, syndecan-1, leptin, adiponectin), using commercially available ELISAs and Luminex kits, immunological tests (T cell phenotype and functional analysis), and immunometabolism (AMPK phosphorylation). RNA will be extracted from a blood sample collected on study day 2, and will be sequenced to investigate gene expression in the metformin treatment group in comparison to the non-treatment group.

At day 28 of illness, final routine (FBC, biochemistry) and research blood samples will be taken to check whether patients have fully recovered from the acute dengue episode.

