### Statistical considerations

***Sample size.*** This is an exploratory study focusing primarily on safety, and there are no preliminary data regarding the effects of metformin in dengue on which to base a sample size calculation. A target sample size of 60 patients was chosen based on clinical judgement and feasibility considerations. Using the trend in VCAM over time, which is one of the secondary endpoints, by assuming a slope of change in concentration over time at 0.34 (log
_2_VCAM concentration per day, data based on biomarkers of endothelial function in dengue), we conducted a power calculation using a t-test to compare effects on endothelial function between two groups. It is suggested this study will have a power of 80% to detect a difference of at least 0.023 (log
_2_VCAM concentration per day) in the slope of change.

***Statistical analysis.*** The primary analysis population will include all patients from cohort 1 and cohort 2, plus 60 controls as mentioned previously. Baseline characteristics and outcomes will be summarised for each treatment group. The cohort of patients enrolled in this study will form the active treatment group, while the control group will consist of overweight and obese dengue patients that participated in a matched cohort observational study, none of whom received metformin therapy. Continuous variables will be described using medians and quartiles, while categorical variables will be described in terms of frequencies and percentages.

The primary endpoint (number of AEs), will be compared between the treatment groups using negative binomial regression model. The clinical, biomarker, immunological will be compared between the treatment arms using linear regression or random effects model for continuous endpoints, and Cox regression for time-to-event endpoints (fever clearance time, time to first undetectable viremia measurement, time to first negative NS1 measurement). All comparisons will be adjusted for age, sex, and day of illness, as patients will not be randomized. For percentage increase in HCT and area under the curve of viraemia, comparisons will be also adjusted for the pre-dose value of the respective marker.

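### The fixed covariate set for the non-randomised comparison leaves out BMI and prior dengue exposure, although the protocol names obesity and prior exposure as risk factors for severe dengue

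*Protocol article*

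**What the plan says.** The comparison is not randomised. Under Design: "The 60 patients receiving treatment will be compared to 60 overweight or obese patients with standard of care", the controls coming from a separate observational study that is running at the same time with the same enrolment criteria.

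Under Statistical considerations, the primary analysis is set out as follows: "The primary endpoint (number of AEs), will be compared between the treatment groups using negative binomial regression model". The covariates for this and every other comparison are then fixed: "All comparisons will be adjusted for age, sex, and day of illness, as patients will not be randomized". Two secondary endpoints, percentage increase in haematocrit and area under the viraemia curve, receive one further term: "comparisons will be also adjusted for the pre-dose value of the respective marker". The primary endpoint receives nothing beyond the three covariates.

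On prognosis, the Background lists groups at particular risk of severe dengue, "and those with prior exposure to alternative dengue serotypes" among them, and goes on to name obesity as a further risk factor. On data, BMI (or BMI-for-age) is an entry criterion, and under Data collection "Serology tests (Capture IgM/IgG ELISAs) will be performed on enrolment (acute) and discharge/FU (convalescent) samples".

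On the control group, the Abstract says that treated patients will be "compared to a non-treated group of 60 age-matched overweight and obese dengue patients". The recruitment text describes no matching step.

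**The concern.** The protocol gives the lack of randomisation as its reason for adjusting. The set ought then to contain the measured factors that the protocol itself regards as prognostic. Two of them are absent.

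The omission reaches the primary endpoint because of what that endpoint counts. Table 1 includes a fall in pulse pressure or systolic pressure, mucosal bleeding, a large rise in transaminases and very low platelets. Each of these can be the disease rather than the drug. If one group holds more patients at high risk of severe dengue, it can accrue more events with no drug effect. If the treated group holds fewer, real harm can be masked. For a safety endpoint both errors matter.

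The BMI entry threshold does not make BMI redundant. It is a lower bound without an upper one, so overweight and markedly obese patients are pooled. Leptin and adiponectin, which the Background describes as adipocyte products, are also secondary endpoints.

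**Working it through.** The protocol gives no power or precision figure for the AE comparison, so there is nothing of its own to reproduce. Its one power statement concerns the VCAM slope and has no bearing here.

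**Inputs from the documents:** 60 treated and 60 control patients; negative binomial model for AE counts; covariates age, sex and day of illness.

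**Inputs assumed, because the documents do not give them:** prevalence of the omitted factor in each group; its AE rate ratio, g = 1.5, 2 or 3; for precision, a mean of 1.5 AEs per patient and dispersion 0.5.

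**Step 1. Imbalance by chance.** For a factor with 50% prevalence, the SD of the difference in proportions is √(2 × 0.25/60) = 0.091, or 9.1 percentage points. The 95% range is ±1.96 × 9.1 = ±17.9 points. If two-week blocks induce clustering with an assumed design effect of 1.5 to 2, it widens to about ±22 to ±25 points. A 20-point gap is 20/9.1 = 2.2 SD under simple sampling. That is at the edge of what chance produces.

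**Step 2. Shift in the rate ratio.** With the factor left out and a true rate ratio of 1.0, the apparent ratio is

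[1 + p₁(g − 1)] / [1 + p₀(g − 1)],

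where p₁ and p₀ are the prevalences in treated and control patients.

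| g | Treated 60%, control 40% | Treated 40%, control 60% |
|---|---|---|
| 1.5 | 1.30/1.20 = 1.08 | 1.20/1.30 = 0.92 |
| 2 | 1.60/1.40 = 1.14 | 1.40/1.60 = 0.88 |
| 3 | 2.20/1.80 = 1.22 | 1.80/2.20 = 0.82 |

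At a 1-SD gap (54.6% v 45.4%) and g = 2 the ratio is 1.546/1.454 = 1.06. With equal prevalence it is exactly 1.

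**Step 3. Against the precision of the estimate.** Under the assumed mean and dispersion, the SE of the log rate ratio is √[2 × (1/1.5 + 0.5)/60] = 0.197. The 95% margin is then a factor of exp(1.96 × 0.197) ≈ 1.47, say 1.5. On the log scale the shifts of 1.08, 1.14 and 1.22 are about 20%, 33% and 49% of ln 1.5.

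**Step 4. Simulation.** 1,000 trials per scenario, 60 v 60, true rate ratio 1, same assumed mean (in patients without the factor) and dispersion. The model held treatment alone or treatment plus the factor. The prevalence difference was built in as systematic.

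| g | Control v treated | Ratio, factor omitted | Type I error, omitted | Ratio, included | Type I error, included |
|---|---|---|---|---|---|
| 1.5 | 50% v 68% | 1.07 | 7.0% | 1.00 | 4.4% |
| 2 | 50% v 60% | 1.06 | 7.7% | 1.00 | 4.6% |
| 2 | 50% v 68% | 1.11 | 11.4% | 0.99 | 5.1% |
| 2 | 40% v 70% | 1.23 | 22.6% | 1.01 | 4.5% |

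Adding the factor restores both the estimate and the error rate. The rows show what an imbalance of that size would do. They do not show that one will occur.

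**The case against.** The strongest reply is that the design already deals with this. Under Screening, enrolment and retention, the two studies share criteria, wards, standard of care and season. Only one study recruits in any two-week block, and a patient who declines or fails screening for one is barred from the other. This is a real safeguard, chiefly against calendar and ward differences and against steering patients between studies. It does not equalise immune status or BMI between those who accept a drug and those who accept observation, nor does it prevent blocks from differing by chance.

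A second reply is that chance imbalance is already reflected in the confidence interval, and that systematic imbalance is not shown. Both statements are right. A reader might infer that differential consent makes imbalance beyond chance likely; nothing in the documents links willingness to take metformin with immune status or BMI. The case rests on the protocol's own reason for adjusting.

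Third, the effect of BMI within this population is unknown. The odds ratio of 1.38 in the Background compares obese with non-obese children on severe dengue. It does not measure variation above the entry threshold, nor AE counts. That stands, and no size is claimed for BMI specifically.

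Fourth, infection status is derivable from the serology, but the article does not say that it will be classified, and the controls' measurements belong to another study that is not shown. The convalescent sample is taken after treatment and may be missing. These points limit the fix without defeating it.

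Finally, the study is exploratory and defers firm conclusions to a later randomised trial. That lowers the stakes, but the comparison of AE counts remains the primary analysis.

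**Conclusion.** The point holds for BMI and prior dengue exposure. The covariate set is fixed in the protocol and omits two factors that the protocol's own account treats as prognostic and for which data are planned, and the gap reaches the primary endpoint. The possible shift is modest to moderate: 8% to 22% on the rate ratio for a 20-point imbalance and an assumed factor effect of 1.5 to 3, and about 6% for a 1-SD imbalance with a doubling of the rate. Every input apart from the group sizes is an assumption. Confounding is possible and cheaply reduced; it is not demonstrated.

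Three stronger readings are not supported:

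- **Serotype.** A reader might infer that infecting serotype is also a named and measured driver of severity. The Background names prior exposure, which is immune status. Serotype shifts are mentioned only as something that same-season enrolment is meant to avoid, and the PCR assays are not said to determine serotype.
- **All endpoints equally exposed.** Haematocrit increase and viraemia area also receive pre-dose adjustment.
- **Age.** The absence of a described matching step might suggest that age is uncontrolled. Age is in every model, so this is a matter of wording only.

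**What to change.** In the statistical analysis paragraph, extend the fixed covariate set of the between-group models, starting with the primary negative binomial model, by two terms:

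- **BMI**, as BMI-for-age z-score in children. Since adults and children are then on different scales, standardise within each age group so that a single term suffices.
- **Primary or secondary infection**, derived from the IgM/IgG serology where it is available in both groups. State the classification rule in advance, and how unclassified patients are handled.

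Use serotype only in a sensitivity analysis, and only if it is determined in both groups, since it could add several terms.

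Either describe how the controls are age-matched or remove the phrase. No adult/child quota need be imposed on the controls: that would alter another study's recruitment for a variable already in the model.

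The cost is about two degrees of freedom in 120 patients, some missing serology classifications, and confirmation that the control study records the same serology. The treated group needs no measurement that is not already planned.

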### Secondary endpoints

The secondary endpoints are: fever clearance time (the time from enrolment to sustained body temperature <37.5°C for 48 hours); platelet nadir and highest AST/ALT between days 3 and 8 of illness; percentage increase in haematocrit (HCT) from baseline (using HCT obtained at the 28 day FU visit to reflect baseline); plasma viraemia (area under the log
_10_-transformed viraemia curve from study days 3 to 6); time from enrolment to first undetectable viraemia and first negative NS1 measurement; trend over time (5 days) in VCAM1, CRP, leptin, adiponectin, low density lipoprotein (LDL), and AMPK phosphorylation; and magnitude of activated/proliferating T and NK cells as well as frequency and phenotype of dengue-specific CD4+ and CD8+ T cells, quantified by flow cytometry at enrolment and hospital discharge.

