### Screening, enrolment and retention

Patients aged between 10 and 30 years that are admitted to one of the three study wards of the HTD, HCMC, Vietnam, with clinical suspicion of dengue and less than 72 hours of fever are invited to participate in the trial. After giving consent, patients are screened for their eligibility to commence treatment with the trial drug by the study physicians. Blood samples are collected to test for NS1, and AST, ALT and creatinine levels and in female patients, a urine sample is collected for a pregnancy test. Glucose and lactate levels are measured using point-of-care (POC) tests.

All patients will be asked to come back for a final FU visit at 28 days after the onset of fever. Patients will be contacted 3–5 days prior to the FU visit to arrange an appropriate appointment date and time. Any case who misses the FU visit will be contacted by phone either to reschedule the visit or to collect information if patients could not arrange their time to come back. If the patients stay in the hospital for longer than 5 days, due to AEs or any other reason, the treatment for these cases will be at discretion of the attending physicians. No further blood samples or study procedures will be performed from this point onward. However, the final outcome at discharge will be collected in the case report form (CRF;
*Extended data*
^46^).

At discharge, the participants will be offered a referral to nutrition specialists for a consultation of overweight/obesity management. Patients will also be provided with leaflets on healthy eating and lifestyle behaviours.

While not an RCT, this trial is designed to enroll patients contemporaneously with an observational obesity trial, where patients received standard care, to minimize systematic differences between the intervention (metformin) and control group, i.e. patients have the same inclusion /exclusion criteria, enrolled on same wards, with the same standard of care during the same dengue season (to avoid the issue of viral serotype shifts). 

To minimize selection bias, we have set up a system on the dengue wards, to ensure eligible patients are recruited into both studies in a systematic way. This involves only one study enrolling for a 2-week time block. During that time, if a patient fails screening assessment or declines enrollment into one of the trials, they are not eligible for the other.

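### Platelet nadir, peak AST/ALT and time to undetectable viraemia are compared without their enrolment values in a non-randomised design, although two other endpoints get this adjustment

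*Protocol article*

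**What the plan says.** The Statistical analysis paragraph of the protocol article sets one covariate list and gives the reason for it: "All comparisons will be adjusted for age, sex, and day of illness, as patients will not be randomized". It then makes one extension, for percentage haematocrit increase and viraemia AUC only: "comparisons will be also adjusted for the pre-dose value of the respective marker".

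The Secondary endpoints section lists further endpoints that have a natural enrolment value but are not in that extension:

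- "platelet nadir and highest AST/ALT between days 3 and 8 of illness";
- "time from enrolment to first undetectable viraemia and first negative NS1 measurement";
- T- and NK-cell measures, "quantified by flow cytometry at enrolment and hospital discharge".

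The enrolment data are planned. At screening, "Blood samples are collected to test for NS1, and AST, ALT and creatinine levels". The Laboratory evaluation paragraph plans a daily full blood count, with daily viraemia measured on the residual blood. BMI is needed for eligibility, but it is not among the covariates.

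**The concern.** The protocol accepts that adjustment is needed because allocation is not random, and it accepts that a marker's own starting value matters for two endpoints. The same reasoning applies to the three endpoints left out. Viraemia shows the inconsistency most clearly: its AUC is adjusted for the starting level and its clearance time is not, although a patient who starts higher has further to fall. For platelets and transaminases, entry is within 72 hours of fever onset and the outcome window opens on illness day 3, so the enrolment value can itself lie inside the window.

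Age, sex and day of illness do not stand in for how ill a patient already is at entry. The Discussion says that, if safety is established, improvement in any secondary endpoint would justify a larger randomised trial. A baseline difference in one unadjusted marker could therefore feed directly into that decision.

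**Working it through.** **Reading the text.** The covariate rule, set against the endpoints, gives:

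| Endpoint | Enrolment value collected | Adjusted for it |
|---|---|---|
| Percentage HCT increase | yes | yes |
| Viraemia AUC | yes | yes |
| Time to undetectable viraemia | yes (same marker) | no |
| Platelet nadir | yes (full blood count) | no |
| Highest AST/ALT | yes (screening) | no |
| Time to negative NS1 | positive in everyone; no quantitative assay described | no |
| T/NK cells | yes, part of the endpoint | depends on the model, which is not fixed |

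**The plan's own figure.** The only computed figure in the section is 80% power for a VCAM slope difference of 0.023 log2 units per day. No SD is given, so it can only be inverted: with 60 per group and two-sided 0.05, the implied SD is about 0.045. It does not bear on the covariate list and is not used below.

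**Illustration for the linear models.**

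- From the document: n = 60 per group.
- Assumed: two-sided 0.05; no true effect; outcome and baseline in SD units; correlation r = 0.5–0.7 remaining after age, sex and day of illness; baseline difference d = 0.3 SD.

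1. Standard error of the unadjusted difference: √(2/60) = 0.183 SD.
2. Bias = r × d: 0.5 × 0.3 = 0.15 SD; 0.7 × 0.3 = 0.21 SD.
3. Residual variance after adjustment = 1 − r²: 0.75 and 0.51, a fall of 25% and 49%.
4. Difference detectable with 80% power: 2.80 × 0.183 = 0.511 SD unadjusted; multiplied by √0.75 or √0.51, it is 0.443 or 0.365 SD.
5. False-positive rate if the 0.3 SD is a **systematic** difference between the two source populations: Φ(bias/SE − 1.96) + Φ(−bias/SE − 1.96). With bias/SE = 0.82 this is 13.0%; with 1.15 it is 21.0%.
6. False-positive rate **given a chance imbalance** of 0.3 SD: once the baseline difference is fixed, the standardised group difference has variance 1 − r², not 1. So P(|N(bias/SE, 1 − r²)| > 1.96). For r = 0.5 the main tail is Φ(−(1.96 − 0.82)/0.866), and both tails give 9.5%. For r = 0.7 it is Φ(−(1.96 − 1.15)/0.714), giving 12.8%.
7. How often chance alone gives at least 0.3 SD: 0.3/0.183 = 1.64, or about 10% of trials of this size.

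**Sensitivity to the assumptions.** For a systematic difference of 0.2 SD, the rate is 6.2%, 8.5% and 12.0% at r = 0.3, 0.5 and 0.7. For 0.5 SD it is 13.0%, 27.8% and 48.3%.

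**The case against.** The design already limits imbalance. Eligibility is shared, both groups come from the same wards and season, enrolment alternates in two-week blocks, and severe dengue, AST/ALT above 250 U/L and lactate above 2.0 mmol/L are excluded. These controls narrow the baseline range and make a large systematic difference less likely. They do not guarantee balance at 60 versus 60, and the protocol's own covariate list concedes as much. Age is the only matching variable named.

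It can also be said that covariates for exploratory secondary endpoints belong in the SAP. Here, though, the protocol fixes the common list and names the two endpoints that get the extra term. That is a stated choice, not an omission.

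Some stronger readings are tempting, but the documents do not support them:

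- **NS1 clearance lacks its own baseline.** Every patient is NS1 positive at entry and no quantitative assay is described, so a positive/negative enrolment value carries no information. Enrolment viraemia can serve only as a prognostic covariate.
- **T/NK cells are unadjusted.** The endpoint includes the enrolment measurement, and a random effects model is allowed. The gap exists only if discharge values are compared by linear regression.
- **Omitting BMI confounds leptin, adiponectin and CRP.** These are analysed as five-day trends. A BMI effect on level does not distort a slope, and a BMI main effect would not repair a BMI-by-time effect. The odds ratio of 1.38 in the Background compares obese with non-obese children, so it is not a gradient within this overweight and obese sample.
- **The overall type I error is 13–21%.** That range needs a systematic 0.3 SD difference, for which the documents give no evidence. Averaged over chance imbalances alone, the rate stays at 5%.
- **The precision gain applies to every endpoint.** The variance arithmetic is for linear models and does not carry over to the Cox endpoints.

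**Conclusion.** The point holds for platelet nadir, highest AST/ALT and time to first undetectable viraemia. The covariate rule leaves out enrolment values that the trial collects, and it treats viraemia inconsistently. The likely harm is moderate. Under the assumed correlation and a 0.3 SD difference, the bias is 0.15–0.21 SD. The false-positive rate is about 13–21% if the difference is systematic and about 9–13% given a chance imbalance of that size. Both the correlation and the size of the difference are assumptions. Adjustment removes the bias from a marker only as far as a single enrolment value captures it and the model form is right; other confounding remains.

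The case for BMI is weaker. Eligibility sets only a floor, so BMI above it may differ between groups, but no size can be shown for leaving it out. These are mainly secondary endpoints of an exploratory trial, so the change is advisable and does not decide whether the trial is sound.

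**What to change.** Extend the sentence on pre-dose adjustment before outcome data are seen, and define the value as the enrolment value, since controls receive no dose:

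- enrolment platelets in the platelet-nadir model;
- log screening AST and log screening ALT in the respective peak models;
- enrolment log10 viraemia in the Cox model for viraemia clearance and, as a prognostic covariate, in the Cox model for NS1 clearance;
- the enrolment value in any T/NK-cell comparison made at discharge by linear regression.

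As a secondary step, add BMI on a scale common to adults and children, for example a z-score, to the list that now reads "adjusted for age, sex, and day of illness". Apply it to comparisons of levels, event times and the AE count.

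The cost is a sentence or two of text and one or two degrees of freedom per model, which 120 patients can bear. No new data are needed.
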